**Methods/Design:**

To compare the effectiveness of acupuncture plus lifestyle modification, a 2-armed, controlled trial with randomization using minimization will be conducted on 150 simple obesity and overweight patients, aged 18–50 years, for a 36-week study duration. All patients will be randomly assigned to one of two groups and will receive either acupuncture plus lifestyle modification or lifestyle modification alone. Outcomes will be evaluated at baseline and at 4 weeks, 8 weeks, and 12 weeks during treatment as well as at 6-week, 12-week, and 24-week follow-up. The primary endpoint is change of body mass index (BMI) during the 12th week. Secondary endpoints are body weight; waist-to-hip ratio; biochemical tests including serum cholesterol (TC), triglyceride (TG) and high-density lipoprotein (HDL) levels; and answers to the Short Form 36 (SF-36) and the Impact of Weight on Quality of Life Questionnaire-Lite Version (IWQOL-Lite). Statistical analyses will be based on the intention-to-treat (ITT) principle. The main endpoint will be analyzed by analysis of covariance (ANCOVA), and the objective outcome results will be analyzed by logistic regression analysis. To avoid potential confounding factors, additional sensitivity analyses will be conducted following these statistical analyses.

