#### Outcomes

The primary outcome is the change of BMI during the 12th week after minimization. The formula for BMI is as follows:

BMI = mass (kg)/(height(m))^2^.

The BMI of all patients will be calculated at baseline; during treatment at 4, 8, and 12 weeks; and 6-week, 12-week, and 24-week follow-up [39]. The BMI reduction will be assessed by a blinded investigator from the Clinic of Nanjing University of Chinese Medicine.

The secondary outcomes are divided into objective outcomes and patient-centered outcomes. The body weight and the waist-to-hip ratio will be used as supplementary measures in combination with the BMI, and will be calculated at baseline; during treatment at 4, 8, and 12 weeks; and at 6-week, 12-week, and 24-week follow-up. In addition, TC, TG, and HDL levels also will be tested at baseline; during treatment at 4, 8, and 12 weeks to assess the metabolic changes [40]. For patient-centered outcomes, IWQOL-Lite and SF-36 are used to measure obesity-specific quality of life. The IWQOL-Lite questionnaire is a validated, obesity-specific measure, consisting of 31 items regarding the impact of obesity on physical function, self-esteem, sexual life, public distress, and work [41–43]. Patients will be asked to rank items related to obesity in 5 areas, ranging from 5 “always true” to 1 “never true”, by an independent assessor. The independent assessor will give a detailed explanation regarding every item of this questionnaire to patients before the treatment. All the patient-centered outcomes will be detected before treatment; during treatment at 4, 8, and 12 weeks; and at 6-week, 12-week, 24-week follow-up. Adverse events and serious adverse events will be recorded during the study to assess safety. By using a valid expectation questionnaire relating to acupuncture [44], participants’ expectations for acupuncture at baseline will also be assessed.

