### Statistics

#### Sample size calculation

The sample size was determined prospectively as described in a previous study that used similar outcome measurements [45]. The following formula was used to estimate the sample size:$$ n=\frac{{\left({u}_{\alpha }+{u}_{\boldsymbol{\beta}}\right)}^2\kern0.5em \left( 1+ 1/k\right){\sigma}^2}{\delta^2} $$

An independent statistician will monitor the study design from the beginning of the study and take responsibility for calculating the sample size and all data. Acupuncture treatment is reported to cause a 4.84 ± 7.38 (mean ± standard deviation) kg reduction of body weight compared to lifestyle modification treatment alone, according to a previously published systematic review [12]. This study was designed to have 80 % power and a significance level of 5 % for the purpose of discriminating differences between electro-acupuncture plus lifestyle modification and lifestyle modification alone. To achieve this, 64 patients will be included in each group and a total number of 150 patients will be enrolled, allowing for a 15 % dropout rate per group.

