#### Analysis

The primary outcome is the change of BMI during the 12th week after minimization. To determine differences between the 2 groups after 12 weeks, analysis of covariance (ANCOVA) will be used to adjust for baseline values. Because there are two primary analyses (electro-acupuncture plus lifestyle modification versus lifestyle modification alone), Bonferroni correction will be used to address multiple testing, and a significance level of 0.05 will be used.

Statistical analyses of primary and secondary outcomes will be conducted as follows. First, all the analyses will be based on the intention-to-treat (ITT) principle. All patients, who will provide baseline data, will be included in the analyses, regardless of whether or not they complete the treatment or adhere to the protocol. Data distribution is expected to be normal, and skewed distribution data will be transformed prior to analysis. The statistical hypotheses are:

H_0_: acupuncture plus lifestyle modification = lifestyle modification (null hypothesis) versus H_1_: acupuncture plus lifestyle modification ≠ lifestyle modification (alternative hypothesis).

ANCOVA will be subsequently performed on BMI, body weight, and waist-to-hip ratio data as well as SF-36 and IWQOL-Lite. SF-36 and IWQOL-Lite will be transformed to continuous variables before analysis. Missing values will be addressed using the methods of last observation carried forward (LOCF). To address the results of objective outcomes, logistic regression analysis will be used to analyze dependent variables, including TC, HDL, and TG levels. These statistical analyses will be performed using SPSS 15.0 statistics software (SPSS Inc., Chicago, IL, USA) and SAS 9.0 (SAS Institute Inc., Cary, NC, USA).

To avoid potential confounding factors, additional sensitivity analyses will be conducted following these statistical analyses by using STATA (StataCorp, College Station, TX, USA) or R methods. Patient expectations also will be included as ordinal fixed factors in the sensitivity analyses. Full analysis set and the potential confounding factors relating to baseline differences will be used to calculate the results.

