The main challenge of this trial is to innovate a pragmatic study protocol uniting personalized acupuncture treatment with advanced research methodologies. To resolve this challenge, a dimensional study group, including a renowned acupuncture professor, skilled acupuncturists, nutritionists, clinical methodologists, physicians, and patients, was built before the study began. Each aspect of the study design was fully discussed and revised by this group. Since the populations of obese and overweight adults in China have climbed to 12.0 % and 30.6 %, respectively, both obese and overweight patients will be enrolled in this study, reflecting those who usually receive treatment for weight-loss in terms of a pragmatic design. Lifestyle modification is the cornerstone among all the obesity treatments currently available. We therefore employ acupuncture plus lifestyle modification as an intervention in this trial, facilitating the real-world clinical treatment of obesity. To evaluate patient-reported outcomes, the IWQOL-Lite questionnaire will measure the impact of obesity on dimensional aspects of life. This questionnaire has been made by researchers at Duke University and has been used successfully in many obesity trials [47–50]. To monitor the food intake of overweight and obese patients, a 24-hour food recall diary will be applied to record mean nutrient intake during 24 hours. This diary is a valid instrument for estimating nutrition intake and a beneficial tool for self-monitoring of dietary intake. It has been proved and performed in numerous nutrition researches [32–34]. Moreover, minimization will be conducted as a random procedure in this trial, avoiding possible confounding factors such as different obesity levels, gender, and age. Additionally, an Internet social network will be established and be used throughout the study, promoting the persistence of treatment for patients during treatment and follow-up phases.

As this trial refers to two clearly different treatments, blinding is hard to perform after minimization. Hence, a limitation of internal validity and multiple potential biases, including expectations of the patients and providers, may occur during this study. To minimize these potential biases, most of the outcomes in this trial are designed to be objective outcomes, such as BMI, body weight, waist-to-hip ratio, and biochemical tests.

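### Logistic regression is prescribed for TC, HDL and TG, which the protocol defines only as continuous levels, so the stated model does not fit these secondary outcomes

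*Protocol article*

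**What the plan says.** The Analysis section of the protocol article deals with the lipids in one sentence: "logistic regression analysis will be used to analyze dependent variables, including TC, HDL, and TG levels". The abstract (Methods/Design) gives the main endpoint to ANCOVA and then adds that "the objective outcome results will be analyzed by logistic regression analysis".

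The Outcomes section describes the lipid outcomes as follows: "TC, TG, and HDL levels also will be tested at baseline; during treatment at 4, 8, and 12 weeks to assess the metabolic changes". No section names a cut-off, an abnormal range or a responder rule for any of the three.

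For the remaining outcomes the Analysis section says that "ANCOVA will be subsequently performed on BMI, body weight, and waist-to-hip ratio data as well as SF-36 and IWQOL-Lite". It also sets a general rule for distributions: "Data distribution is expected to be normal, and skewed distribution data will be transformed prior to analysis". The Discussion states that "most of the outcomes in this trial are designed to be objective outcomes, such as BMI, body weight, waist-to-hip ratio, and biochemical tests".

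**The concern.** Binary logistic regression models the probability of falling in a category. TC, HDL and TG appear in this protocol only as measured levels, collected to show metabolic change. The outcome and the model therefore do not match. An analyst who follows the text must either cut each lipid at a value the protocol does not give or use a different model.

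Cutting the variable would change the question from how far the level moved to what share lies beyond a line. It would also discard information, and the result would depend on where the line falls.

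A second, smaller problem is that the abstract's wording reaches further than the Analysis section does. Some outcomes that the Analysis section sends to ANCOVA also belong to the class that the abstract sends to logistic regression.

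**Working it through.** **Model against outcome**

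| Outcome | How it is defined | Analysis section | Abstract |
|---|---|---|---|
| BMI | continuous; primary | ANCOVA | ANCOVA (main endpoint) |
| Body weight, waist-to-hip ratio | continuous; secondary; objective according to the Discussion | ANCOVA | logistic, if read as objective outcomes |
| TC, HDL, TG | continuous levels; secondary; objective according to the Discussion | logistic | logistic |
| SF-36, IWQOL-Lite | converted to continuous | ANCOVA | not stated |

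The lipids are the only outcomes for which the Analysis section pairs a continuous measure with a model for categories. The section's rule of expecting normality and transforming skewed data is a rule for continuous data, so the lipids could be handled under it without a different model. The Outcomes section divides the secondary outcomes into objective and patient-centred ones. Body weight and waist-to-hip ratio are not patient-centred there, and the Discussion lists them as objective by name. The overlap between abstract and Analysis section therefore concerns these two outcomes.

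**Cost of cutting a continuous lipid (illustration)**

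The protocol states no lipid effect, SD or power, so there is no lipid figure to reproduce. Its only planning inputs concern body weight: "Acupuncture treatment is reported to cause a 4.84 ± 7.38 (mean ± standard deviation) kg reduction of body weight".

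Inputs taken from the protocol:
- 64 per group and 1:1 allocation.
- Two-sided 5 %. The level is in the sample size section ("This study was designed to have 80 % power and a significance level of 5" per cent), and the alternative hypothesis is two-sided.

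Assumed inputs:
- A normal outcome with equal SDs.
- A shift d of 0.5 or 0.3 SD.
- The share p0 of controls beyond the cut, with treatment lowering that share.
- No covariates on either scale.

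Continuous scale: power = Φ(d/√(2/64) − 1.960), with √(2/64) = 0.1768.
- d = 0.5: Φ(2.828 − 1.960) = 0.807. The t-test version gives 0.801.
- d = 0.3: Φ(1.697 − 1.960) = 0.396.

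Cut scale: p1 = Φ(Φ⁻¹(p0) − d), and power = Φ((|p0 − p1| − 1.960·SE0)/SE1). SE0 uses the pooled proportion and SE1 the separate proportions.

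For a median cut, midway between the groups, at d = 0.5:
- The shares are Φ(0.25) = 0.599 and 0.401, a difference of 0.197.
- SE0 = 0.0884 and SE1 = 0.0866.
- Power = Φ((0.1974 − 0.1732)/0.0866) = 0.610. With SE1 used throughout it is 0.625.

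| Cut | Shares at d = 0.5 | Power, d = 0.5 | n per group for 80 %, d = 0.5 | Power, d = 0.3 |
|---|---|---|---|---|
| none (continuous) | – | 81 % | 63 | 40 % |
| median | 0.599 v 0.401 | 61 % | 100 | 27 % |
| 30 % of controls beyond | 0.300 v 0.153 | 51 % | 126 | 23 % |
| 20 % beyond | 0.200 v 0.090 | 42 % | 160 | 20 % |
| 10 % beyond | 0.100 v 0.037 | 29 % | 256 | 15 % |

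The result also depends on direction. At d = 0.5 with the cut 1 SD above the control mean, power is about 38 % if treatment lowers the share beyond it and about 53 % if treatment raises it (SE1 throughout).

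**The case against.** The strongest reply is that a journal article condenses the plan, and that thresholds may sit in a statistical analysis plan that is not shown. That is fair as far as the missing threshold goes, and the missing threshold alone would not be a finding. It does not rescue the sentence, however. The article names the levels themselves as the dependent variables. A plan that added cut-offs would answer a different question from the change described under Outcomes, and a plan that used ANCOVA would contradict the article. An ordinal logistic model on the raw values is technically possible, but nothing in the text describes one.

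A reader might also infer more than the protocol supports:
- **That the primary analysis is affected.** It is not. The abstract and the Analysis section both give BMI to ANCOVA, and BMI is the main endpoint even though the Discussion lists it among the objective outcomes.
- **That a cut-off would be picked with the data in view.** Nothing says when or how one would be chosen, and the Blinding section keeps the statistician blind to group identity until the end of the study. All that can be said is that no threshold is declared.
- **That logistic regression leaves the baseline value unused.** A logistic model can carry the baseline lipid as a covariate, and the article does not list that model's covariates.
- **That the power figures are this trial's losses.** They rest on assumed effects and cuts.

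**Conclusion.** The point holds as a mismatch between model and outcome for three named secondary outcomes. It comes with a wording conflict between the abstract and the Analysis section over body weight and waist-to-hip ratio. As written, the model cannot estimate the change in lipid level that the Outcomes section sets out to assess.

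If the mismatch were resolved by cutting the lipids, an effect with about 80–81 % power at 64 per group would fall to roughly 61–62 % at best, and to 29–51 % for cuts that leave 10–30 % of controls beyond them. For a 0.3 SD effect the fall is from about 40 % to 15–27 %. These ranges assume normality, equal SDs, treatment lowering the share beyond the cut, and effect sizes that the protocol does not supply. The textual finding does not depend on them.

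This should be fixed, but it does not threaten the trial's main conclusion.

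**What to change.** In the Analysis section, move TC, HDL and TG into the list of outcomes analysed by ANCOVA: the week-12 value compared between groups, adjusted for the baseline value, and transformed if skewed under the rule already stated there. Report mean differences with 95 % confidence intervals, or ratios of geometric means if a log transformation is used. Amend the abstract's sentence so that it no longer assigns logistic regression to the objective outcomes as a class.

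If a binary lipid endpoint is also wanted, keep logistic regression as a supplementary analysis and state one threshold per lipid before unblinding.

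The cost is wording in two places. Baseline and week-12 lipids are already scheduled, so no new data are needed. The change should be documented before the groups are unblinded.

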#### Safety monitoring

Routine tests, including blood, urine, and stool sample analyses, electrocardiogram, and abdominal B ultrasound, will be performed on all patients before minimization. These test results will be part of the inclusion and exclusion evidence screened by a general physician. Acupuncture adverse events are defined as bleeding, fainting, hematoma, serious pain, and local infection. All adverse events, as well as managing these events, will be carefully recorded during the treatment and in the follow-up phases.

#### Quality control

A diverse study group including the principal investigator, recruiters, acupuncturists, nutritionists, data manager, monitor, and patients will be established before the study. All of them contribute to the design of this study. Basic study training to understand the design, purpose, and basic information will be performed before the study. In addition, an independent data manager will be responsible for saving and managing the various data. A checklist including all the important aspects during the study will be made, and a trained monitor will check this checklist and report the quality assurance throughout the trial in accordance with the protocol. Acupuncturists and nutritionists will be free to conduct individualized treatment for each patient due to the pragmatic trial design. Therefore, a few procedures will be undertaken to inspect their treatment. Patient withdrawal and adverse events during the study will be recorded in detail. Regular team meetings will be held and fully documented.

#### Regulatory and ethics approval

This study was approved by the Chinese Ethics Committee of Registering Clinical Trials (ChiECRCT-2012012) and is in compliance with the common guidelines for clinical trials (Helsinki Declaration). The registration number of this trial is ChiCTR-TRC-12002762. All recruited patients will obtain and sign an informed consent form.

## Discussion

For the first time, this study will evaluate the effectiveness of a combined intervention including both acupuncture and lifestyle modification for treating obesity in comparison with lifestyle modification alone in a normal clinical setting. The aim of this study is to conduct a pragmatic trial which not only will improve the methodology of acupuncture trials on obesity in China but also develop beneficial acupuncture strategies for obesity treatment favoring real-life practical settings. This protocol is in accordance with the STRICTA [22], the Effectiveness Guidance Document (EGD) for acupuncture research [46] and the extension of the CONSORT statement for reporting pragmatic trials [18]. The checklist for Comparative Effectiveness Research (CER) relevant aspects for acupuncture clinical studies has been checked before the study begins.

The main challenge of this trial is to innovate a pragmatic study protocol uniting personalized acupuncture treatment with advanced research methodologies. To resolve this challenge, a dimensional study group, including a renowned acupuncture professor, skilled acupuncturists, nutritionists, clinical methodologists, physicians, and patients, was built before the study began. Each aspect of the study design was fully discussed and revised by this group. Since the populations of obese and overweight adults in China have climbed to 12.0 % and 30.6 %, respectively, both obese and overweight patients will be enrolled in this study, reflecting those who usually receive treatment for weight-loss in terms of a pragmatic design. Lifestyle modification is the cornerstone among all the obesity treatments currently available. We therefore employ acupuncture plus lifestyle modification as an intervention in this trial, facilitating the real-world clinical treatment of obesity. To evaluate patient-reported outcomes, the IWQOL-Lite questionnaire will measure the impact of obesity on dimensional aspects of life. This questionnaire has been made by researchers at Duke University and has been used successfully in many obesity trials [47–50]. To monitor the food intake of overweight and obese patients, a 24-hour food recall diary will be applied to record mean nutrient intake during 24 hours. This diary is a valid instrument for estimating nutrition intake and a beneficial tool for self-monitoring of dietary intake. It has been proved and performed in numerous nutrition researches [32–34]. Moreover, minimization will be conducted as a random procedure in this trial, avoiding possible confounding factors such as different obesity levels, gender, and age. Additionally, an Internet social network will be established and be used throughout the study, promoting the persistence of treatment for patients during treatment and follow-up phases.

As this trial refers to two clearly different treatments, blinding is hard to perform after minimization. Hence, a limitation of internal validity and multiple potential biases, including expectations of the patients and providers, may occur during this study. To minimize these potential biases, most of the outcomes in this trial are designed to be objective outcomes, such as BMI, body weight, waist-to-hip ratio, and biochemical tests.

In summary, this is a pragmatic study design with a focus on the effectiveness of acupuncture plus lifestyle modification for treating obesity. It is our hope that this study is a useful attempt to advance the methodology of acupuncture trials, and the results may disclosure novel evidence for the effectiveness of acupuncture on obesity.

## Trial status

This study is recruiting patients.

## Abbreviations

ANCOVA: analysis of covariance
BMI: body mass index
CER: Comparative Effectiveness Research
CI: confidence interval
CONSORT: Consolidated Standards of Reporting Trials
DALYs: Disability-adjusted Life-Years
EGD: Effectiveness Guidance Document
GCP: Good Clinical Practice
HDL: high-density lipoprotein
LOCF: last observation carried forward
SF-36: Short Form 36
ITT: intention-to-treat
IWQOL-Lite: Impact of Weight on Quality of Life Questionnaire
PCOS: polycystic ovary syndrome
SMS: short message service
SOPs: standard operating procedures
STRICTA: Standards for Reporting Interventions for Controlled Trials of Acupuncture
TC: serum cholesterol
TCM: traditional Chinese medicine
TG: triglyceride
